### Participant timeline {13}

The participant timeline is presented in Table 2.

**Table 2 Tab2:** SPIRIT figure

Timepoint	Study period						
	Enrolment	Day of intervention	Post-allocation				
	−4–18 weeks	0	1 day	3 months	1 y	2y	5y
Enrolment							
Eligibility screen	X						
Informed consent	X						
Allocation	X						
Interventions							
Laminectomy or laminectomy with fusion		X					
Assessments							
Baseline variables	X						
Follow-up variables					X	X	X
X-ray	X				X	X	X
MRI	X			X			X
CT	X		X	X			X

### Sample size {14}

Based on data from the national Swedish spine registry on patients with CSM, reoperation was estimated to be 3.5% after stand-alone laminectomy and 7.4% after laminectomy and fusion. Five-year mortality was estimated to be 16.3% in the same population [31].

We further determined that excluding a 5% excess rate of reoperation in the laminectomy group vs laminectomy and fusion was a clinically relevant target for the study and therefore set the non-inferiority margin at 5 percentage points (pp).

With a planned sample size of 300 participants and with regard to mortality and an additional 5% loss due to dropout and emigration, we end up with 236 analyzable patients. This results in a power of 86% based on simulation using rerandomization. The reason for stopping at 300 patients was made on the calculation on how many patients it is reasonable for the four sites to include in 4–5 years. Ideally, we would have reached for 90% power but have agreed to compromise with a power over 85% if that means that we will finish the study in due time.

All statistical analyses were performed in R [32], version 4.0.5 (R Foundation for Statistical Computing, Vienna, Austria), and the R code used in the sample size calculation may be received upon request.

### Recruitment {15}

Patients with CSM are referred by a general practitioner to a consulting spine surgeon at a large center. Four large spine centers in Sweden are participating in the trial with patient enrolment to secure the reach of the target sample size. No specific strategy to promote the recruitment of patients is used.

## Assignment of interventions: allocation

### Sequence generation {16a}

Participants will be allocated to either stand-alone laminectomy or laminectomy and fusion through randomization with a 1:1 ratio using the REDcap software (Research Electronic Data Capture), after informed consent and agreement to be included in the study. After inserting the patient’s personal number into REDcap, the program reports the random allocation of the patient according to the pre-constructed randomization list. The randomization is stratified for center and participant sex, i.e., using separate lists for each center and sex. The allocation sequence utilizes balanced blocks of three different sizes occurring in a random sequence. The principal investigator and study collaborators are blinded to the sequence, the block sizes, and the block sequence.

### Concealment mechanism {16b}

Concealment mechanism is provided by the REDcap software that allows the user to perform randomization without the possibility of knowing the outcome beforehand. The statistician that created the randomization file that was imported to the REDcap randomization module is a separate statistician, not the same as the study statistician, and is otherwise not involved in the study.

### Implementation {16c}

One accountable spine surgeon at each center has individual logging to REDcap and the logon process is with a two-stage verification using logging and mail code. The accountable spine surgeon implements the allocation.

## Assignment of interventions: blinding

### Who will be blinded {17a}

Trial participants will not be blinded after assignment to interventions as they have online access to their medical records by a centrally managed system. Radiographic assessment is not possible to blind.

The outcome assessors and data analysts will be blinded by using a coding system for the participants and treatment groups.

### Procedure for unblinding if needed {17b}

No procedure for unblinding will be needed as all data analyses are performed after the trial is closed.

## Data collection and management

### Plans for assessment and collection of outcomes {18a}

Participant baseline data are collected manually before the intervention and entered into the REDcap software by the study nurse. Baseline data include routine demographics, smoking habits, work status, on sick leave, duration of neck pain, attitude towards returning to work, use of analgesics, fine motor skills, and patient-reported outcome measures (PROMs) including P-mJOA, NDI, EQ-5D, NRS separately for arm and neck pain, and HADS. The surgeon records data electronically including diagnosis, 10-s grip and release test, 10-s foot-tapping test, surgical treatment, surgical levels, neurological impairment, Nurick grading [33], instability, type of implant, operation time, blood loss, and any perioperative complications. Follow-up postal questionnaires and PROMs are sent to the participants after 1, 2, and 5 years, postoperatively, according to Swespine routines [34, 35].

#### Primary outcome

Assessment regarding the primary endpoint will be made at the 1, 2, and 5 years of follow-up (study protocol initiated) or at any timepoint when increased pain, deformity, or neurological deterioration is detected (patient initiated).

#### Secondary outcomes

The P-mJOA (continuous variable) is a self-administered questionnaire with four domains, measuring motor (upper and lower extremities), sensor (upper extremities), and sphincter dysfunction in participants with CSM. The first domain is scored from 0 to 5, the second domain from 0 to 7, and third and four domains from 0 to 3. The maximum score is 18 points, indicating no deficits and the minimum score is 0, total tetraplegia. The minimum clinically important difference (MCID) in mJOA has been reported to be 2 overall with a threshold of 1 in mild myelopathy (mJOA >14), 2 in moderate myelopathy (mJOA 12–14), and 3 in severe myelopathy (mJOA <12) [36]. Consistency between P-mJOA and mJOA is demonstrated with identical mean scores and a SD of 1.5 together with a strong agreement of 0.83 with the use of the intraclass correlation coefficient and the Spearman correlation [37].

The NDI [28] (continuous variable) ranges from 0 to 100% with higher scores indicating severe disability. The MCID is 15–17% [28, 29, 38].

The Nurick scale (categorical variable) has six grades (0–5) based on the “difficulty in walking.”

EQ-5D index (continuous variable) ranges from −0.5 to 1 with higher scores reflecting a better quality of life [34]. The MCID is 0.24 [28].

EQ VAS (continuous variable) ranges from 0 to 100 with higher scores indicating better health.

NRS for neck and arm pain [29] (continuous variable) ranges from 0 to 10, with higher scores indicating more severe pain. The MCID is 2.5 for NRS of the neck and arm [29].

HADS (continuous variable) ranges from 0 to 42 with higher scores indicating more anxiety/depression with a cutoff for depression of >10 p [30].

The satisfaction index (categorical variable) evaluates the participants’ experienced overall result after surgery. The participant is asked “How is your attitude regarding the treatment result.” The alternative answers are “satisfied,” “uncertain,” and “dissatisfied.”

The 10-s grip and release test (continuous variable) is performed with the forearm in pronation and the wrist in mild extension. The participant is asked to grip and release with their fingers as rapidly as possible and the number of completed cycles of movement within 10 s is counted. Both hands are tested separately. The test has been correlated to the JOA score and differences between sex and age groups in the normal population have been set [39].

The 10-s foot-tapping speed test (continuous variable) is performed with the participant sitting on a chair adjusted so that the hip and knee are flexed at 90° and the bilateral soles have contact with the floor. The participant is asked to move their toes up and down, tapping the floor as quickly as possible for 10 s with their heels firmly planted on the floor. The number of completed cycles of movement within 10 s is counted and both feet are tested separately. The test has been correlated to the JOA score, Nurick grade, 10-s grip and release test, and 30-m walking test [40].

All adverse events in both groups will be recorded. The adverse events will be graded according to severity (categorical variable): grade 1, any non-life-threatening complication treated without invasive procedures; grade 2, complications requiring invasive management such as surgical, endoscopic, and endovascular procedures; grade 3, life-threatening adverse events requiring treatment in an intensive care unit; and grade 4, death as a result of complications [41].

The C2–C7 Cobb angle, C2–C7 cSVA, C7 slope, and T1 slope (continuous variables) are all measured on images taken preoperatively and at 1, 2, and 5 years of follow-up [10, 42]. The development of ASP will be monitored. Participants who develop a progressive kyphosis/DJK of more than 40 mm cSVA [9] and/or C2–C7 Cobb < −10° and neurological deterioration/ASP/restenosis will undergo additional magnetic resonance imaging (MRI) and may be subject to supplementary posterior fusion/revision.

Direct costs include hospital stay related to the surgical procedure, implant-related costs, and pain medication usage. Indirect costs include pain medication usage after discharge, societal costs for absence from work, and worker compensation.

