### Objectives {7}

The objective is to perform a non-inferiority study comparing posterior muscle-preserving selective laminectomy with laminectomy and fusion, to evaluate differences in outcome including reoperations, surgical complications, patient satisfaction, functional scores, and late degenerative changes including spondylolisthesis, kyphosis, and ASP.

We hypothesize that posterior muscle-preserving selective laminectomy is at least as successful in treating patients with CSM resulting in fewer reoperations, shorter hospital stay, and faster return to an active life, without reduced patient satisfaction, functional scores, or delayed kyphosis. Long-term follow-up radiographs and magnetic resonance imaging (MRI) are needed to assess differences in the subsequent degenerative changes including spondylolisthesis, kyphosis, and adjacent segment pathology (ASP) to compare the two strategies. Additionally, data from this study may be used to identify risk factors for the poor outcome to guide surgical decision-making.

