### Trial design {8}

The MyRanc study is a multicenter randomized, controlled, parallel-group non-inferiority trial with 300 adult patients allocated in a ratio of 1:1 to two treatment groups: posterior muscle-preserving selective laminectomy (L-group) and laminectomy with instrumented fusion (LF-group).

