#### Posterior decompression and fusion

A midline incision is made over the appropriate levels, defined as the extension of laminectomy without extending beyond C3–C7 [26]. Soft tissue dissection and retraction are performed to identify osseous landmarks. Special care is taken to spare muscle attachments on C2 and C7. Spinal instrumentation is performed with lateral mass or pedicle screws (C3–C7) combined with rod fixation. Laminectomy is performed with a width not extending more than 2 mm outside the dural borders. Facet joint injury should be avoided. Special care is taken to spare the C7 spinous process and the distal half of the C7 lamina [27]. The sagittal alignment is corrected before spinal fixation. No collar or restrictions will be used [25].

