### Outcomes {12}

The primary endpoint is reoperation for any reason at 5 years of follow-up. Reoperation will be considered in case of:Postoperative hematoma or reperfusion injury with neurologic deterioration within hours/days after the primary surgeryChange in sagittal alignment (kyphosis, DJK of more than 40 mm cSVA [9] and/or C2–C7 Cobb < −10°) with corresponding symptoms of camptocormia/increased pain/neurological deteriorationASP defined as degenerative changes on an adjacent level diagnosed with MRI and concomitant symptoms of myelopathy and/or radiculopathyImplant failure (clear radiolucency around >1 screw or rod breakage with increased neck pain and/or neurologic deterioration)Postoperative infection that requires revision surgery

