## Statistical methods

### Statistical methods for primary and secondary outcomes {20a}

All endpoints will be analyzed in the modified intention to treat (mITT) population, defined as randomized patients who are still alive without having emigrated or left the study after 2 and 5 years.

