#### Secondary outcomes

The secondary outcomes will be analyzed using ordinal regression models, adjusted for sex. In addition, each secondary endpoint will be dichotomized and analyzed using logistic regression. The dichotomization will be done by comparing baseline and follow-up data, either based on MCID when applicable or else by defining success as an improvement from baseline. All secondary endpoints will be analyzed at 1, 2, and 5 years of follow-up, but not until the study is closed.

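### The 5-year alignment outcome can miss kyphosis that was surgically treated before the 5-year film, in either arm

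*Protocol article*

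**What the plan says.** All references are to the protocol article.

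- **Trigger and treatment.** Outcomes {12} lists a symptomatic change in sagittal alignment (cSVA above 40 mm and/or C2–C7 Cobb below −10°) among the grounds for considering reoperation. Secondary outcomes, under Plans for assessment and collection of outcomes {18a}, repeats the limits and says that such participants "may be subject to supplementary posterior fusion/revision". Neither text is limited to one arm.
- **What fusion does to the measurement.** For the index fusion, the intervention section states: "The sagittal alignment is corrected before spinal fixation".
- **Alignment outcome.** Outcomes {12} takes cSVA and Cobb angle as change from baseline at 5 years. The Abstract names development of kyphosis, measured as cSVA, as a secondary outcome.
- **Scoring.** Secondary outcomes, under Statistical methods {20a}, dichotomises "either based on MCID when applicable or else by defining success as an improvement from baseline". No MCID is given for cSVA or Cobb. On timing: "All secondary endpoints will be analyzed at 1, 2, and 5 years of follow-up, but not until the study is closed".
- **Analysis set.** "randomized patients who are still alive without having emigrated or left the study after 2 and 5 years". Reoperation is not a reason for removal.
- **Primary endpoint.** "The primary endpoint is reoperation for any reason at 5 years of follow-up".
- **Hypothesis.** Objectives {7} expects fewer reoperations "without reduced patient satisfaction, functional scores, or delayed kyphosis".

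**The concern.** The limits that make a participant a candidate for alignment surgery are expressed in the same quantities that the secondary outcome measures. The participants with the worst symptomatic alignment are therefore the ones most likely to have it changed surgically before the last film. A comparison of the 5-year film with baseline shows where alignment ended after any rescue, not whether kyphosis developed. The hypothesis asks about the second.

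The participant is recorded as a primary failure, but together with hematoma, infection, adjacent segment pathology and implant failure. A reader who wants to know whether either operation leads to delayed kyphosis has to rely on the alignment outcome, which can leave out the treated cases.

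**Working it through.** **1. The plan's own figures.** Inputs from Sample size {14}: 300 participants, 16.3% mortality, 5% other loss, reoperation 3.5% (laminectomy, L) and 7.4% (fusion, LF), margin 5 pp.

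- Analysable: 300 × (1 − 0.163 − 0.05) = 236.1, which reproduces the stated 236, or 118 per arm.
- Power, unpooled normal approximation: SE = √[(0.074 × 0.926 + 0.035 × 0.965)/118] = 0.0294, and Φ[(0.05 + 0.074 − 0.035)/0.0294 − 1.96] = 85.6%, against the stated 86%.

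The sample size and primary test are sound on this check, and this point does not touch them.

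**2. Which treated kyphosis is visible.** Films are scheduled before surgery and at 1, 2 and 5 years (Table 2; Imaging).

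| Kyphosis and its surgery | Scheduled film showing it | Alignment analysis that misses it |
|---|---|---|
| Both before the 1-year film | none | 1, 2 and 5 years |
| Seen at 2 years, operated later | 2 years | 5 years |
| Both between 2 and 5 years | none | 5 years |

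The third row covers 60 − 24 = 36 months without a scheduled film. In every row the 5-year value is postoperative. If it is better than baseline, the participant meets the improvement rule. If it is equal or worse, the participant is not a success, but the kyphosis that prompted surgery is still not in the 5-year value.

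**3. How many participants.** Expected reoperations for any reason: L 118 × 0.035 = 4.1; LF 118 × 0.074 = 8.7. The share done for alignment is not given. Assuming the same share in both arms:

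| Share for alignment (assumed) | L | LF | L if its rate sits at the margin (7.4 + 5 = 12.4%) |
|---|---|---|---|
| 25% | 1.0 | 2.2 | 3.7 |
| 50% | 2.1 | 4.4 | 7.3 |
| 100% | 4.1 | 8.7 | 14.6 |

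**4. Effect on a proportion.** The most that a dichotomised alignment result can move is the reoperation rate itself: 3.5 pp in L and 7.4 pp in LF. This requires every reoperation to be for alignment and every such participant otherwise to score as a success. The net shift would then be 7.4 − 3.5 = 3.9 pp in favour of laminectomy once these cases were counted. If the laminectomy rate were 12.4%, it would be 12.4 − 7.4 = 5.0 pp the other way. The sign depends on rates the trial has yet to observe.

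**5. Effect on a mean.** Assume that a rescue moves cSVA from 40 mm (the limit) to 17 mm (an end of the normal range cited in the Background), a change of 23 mm. The L-arm mean shifts by 23 × 0.035 × share, which is 0.2 mm at a share of 25% and 0.8 mm at 100%. At a rate of 12.4% the range is 0.7 to 2.9 mm. The mean is little affected at the planning rates. A count of kyphosis events is more sensitive, because each missed case is a whole event.

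**The case against.** The strongest case for leaving the plan alone has five parts.

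- **The participant is not lost.** Fusion for kyphosis is a primary-endpoint failure, and surgically managed complications are grade 2 adverse events, which are also compared. This stands. A reader might infer that a failed laminectomy is counted as a success of the trial's main comparison, and the documents rule that out. Neither measure isolates kyphosis, however.
- **Earlier films are analysed too.** This stands in part: deformity present at 1 or 2 years and treated later is captured there. Deformity that arises and is treated between films is not.
- **Both arms are exposed.** This stands. A reader might infer a bias towards laminectomy, because rescue there resembles the comparator while a fused participant cannot cross over to laminectomy alone. The documents do not support that. The rule covers participants in general and includes distal junction kyphosis, which the Background puts at 24% within a year of fusion. More reoperations are also expected after fusion.
- **Scoring as observed is a legitimate treatment-policy choice.** This stands, and it is why that analysis should be kept. It answers how alignment looks after a strategy that includes rescue, whereas the hypothesis also asks whether kyphosis develops.
- **Details may be in an analysis plan that is not shown.** The article never says how values after reoperation are handled, and that silence alone is no finding. The point rests on what is written: the 5-year comparison with baseline, the improvement rule, and an analysis set that retains reoperated participants. That a rescue fusion corrects alignment is an inference, since the sentence on correction describes the index operation.

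**Conclusion.** The point holds for 5-year alignment. As written, that outcome can miss kyphosis treated before the 5-year film, or score it as improvement, in either arm. On the planning rates at most about 4 of 118 laminectomy and 9 of 118 fusion participants are expected to be affected, and probably fewer. These bounds assume that the registry rates of 3.5% and 7.4% apply to the 5-year follow-up. The laminectomy figure would reach about 15 if the true rate sat at the margin. No direction of net bias is shown.

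It does not extend to scoring every reoperated participant as a failure or in the worst category on the patient-reported outcomes, which a reader might take as the logical next step. That would place someone reopened early for a hematoma and fully recovered in the worst 5-year category for pain and function, and would make each secondary outcome partly repeat the primary one. Outcomes {12} also lists most of these measures at 2 years; their 5-year analysis comes only from the statistical section.

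**What to change.** In Secondary outcomes under Statistical methods {20a}, add one prespecified dichotomous outcome for both arms: kyphosis developed, met if cSVA exceeds 40 mm or C2–C7 Cobb is below −10° on any postoperative film up to 5 years, or if a reoperation for alignment has taken place by then. Analyse it with the logistic model already planned and report it beside the as-observed change from baseline. State how participants already beyond a limit at baseline are handled, since Table 1 screens on the modified K-line and not on cSVA or Cobb.

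Keep the patient-reported outcomes as observed, with at most an optional sensitivity analysis. The clinical rule on reoperation and the primary test need no change.

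The cost is a few lines of text and one extra analysis. The films and reoperations are already collected, the indications for reoperation are already to be monitored, and analysis waits until the study closes, so the definition can still be fixed in advance. The downside is that participants whose alignment was successfully corrected still count as having developed kyphosis. That is what this outcome is meant to measure, and the as-observed analysis beside it shows where they ended.

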#### Imaging

Standing radiographs of the cervical spine in neutral, flexion, and extension will be performed preoperatively and at 1, 2, and 5 years of follow-up. When radiographs of the neutral position are executed, the participant will be in a comfortable standing position with the head facing forward for a horizontal gaze. The radiographs will be used to investigate the sagittal alignment by measuring the C2–C7 Cobb angle, C2–C7 cSVA, C7 slope, and T1 slope [16].

MRI of the cervical spine with T1- and T2-weighted images in sagittal and T2-weighted in axial planes will be performed preoperatively, after 3 months and at 5 years of follow-up. Hereby the compression of the spinal cord can be assessed as well as the performed decompression and the degenerative development over time.

Computed tomography (CT) will be performed pre- and postoperatively and at 3 months and 5 years to control the screw fixation, bony anatomy, and fusion (Table 2).

### Plans to promote participant retention and complete follow-up {18b}

Participants that do not reply on the first set of PROMs will get two reminders by mail. If still no response, they will be approached once by telephone. If still no response, information about missing participants that have not left the study will be retrieved from the medical records, radiographs, and the Swedish patient registry.

